#### Control

The comparison group will receive usual care and no SCOHP intervention. As participants will be recruited from a variety of settings (hospital outpatients, community organisations) we anticipate variation in standard care received. To capture this variation, all participants will complete the Health Care Utilisation Questionnaire (HCUQ) [30] at each time point. Participants in the control group will have the option of completing the SCOHP at the end of the trial once evaluation is complete.

#### Outcome measurements

Table 2 details the primary and secondary outcome measures and time points for carers and stroke survivors. Participants complete the measures independently unless a specific request is made for assistance e.g. due to vision or motor skill impairment. Primary outcome measures for both stroke survivors and carers are quality of life and self-efficacy. Health-related quality of life will be assessed using the (AQoL-6D) [25], which consists of six dimensions of health and a global ‘utility’ score and the EuroQol-5D (EQ-5D) [26]. Self-efficacy is to be assessed using the General Self-Efficacy Scale (GSE) [31] a measure of perceived self-efficacy in response to daily challenges and stressful life events. Secondary measures for both stroke survivors and carers are: coping strategies as measured using an abbreviated version of the COPE inventory, the Brief COPE [32]; symptom severity and caseness of depression and anxiety disorders as assessed using the Hospital Anxiety and Depression Scale (HADS) [33]; a 10-item measure of the Big Five personality dimensions (BFI-10) [34]; effect of an individual’s mental health on their ability to function via the Work and Social Adjustment Scale (WSAS) [35]; treatment expectancy and rationale credibility of the clinical study as assessed with the Credibility/Expectancy Questionnaire (CEQ) [36]; perceived satisfactoriness of treatment as assessed using the Treatment Evaluation Inventory-Short Form (TEI-SF) [37]; and health care utilisation and its economic impact assessed by the Health Care Utilisation Questionnaire (HCUQ) [30]. Stroke survivors will also be assessed for cognitive and emotional responses to stroke using the Brief Illness Perceptions Questionnaire (BIPQ) [38]. In addition, carers will be assessed for carer strain using the Modified Caregiver Strain Index (MCSI) [39] and carer satisfaction as assessed by the Carer Assessment of Satisfaction Index (CASI) [40].

Due to the potential for variability of ‘usual care’ in the control group, key aspects of usual care will be assessed with the HCUQ. Furthermore, medical records will be reviewed to determine stroke diagnostic information and clinical indices including the Modified Rankin Scale (MRS), which measures the degree of disability/dependence after a stroke.

#### Program assessment and treatment fidelity

The SCOHP facilitators will be trained in program delivery, receive a structured manual/protocol and monthly group supervision with the clinical investigators (with individual supervision provided as needed in between group sessions). The purpose of supervision will be to discuss problems in study procedures and ensure standardised activity. The SCOHP sessions will be audio recorded with a random selection rated by independent assessors in compliance with the SCOHP protocol. Variations from the protocol will be identified and relayed to the facilitator. Facilitators will complete a summary of each session using a standard template and send these notes to the research team. Session notes will include OHP topics covered, participant concerns raised, and needs for supervision. Additionally, content of sessions regarding participant requirement and concerns will be discussed at supervision meetings.

Post-intervention focus groups will be held for clinicians and participants. Participants will be informed during consent (both written and verbal) of the option to participate in focus groups, and that the purpose is to ascertain an in-depth understanding of their experiences of the study, advantages and disadvantages of conducting the study/program in their services (for clinicians), and recommendations for components to include or exclude from the SCOHP. It will be made clear to participants when consenting that the number of focus groups will be limited; such that they will only be run until data saturation is achieved. It is envisioned that data saturation will be reached after 2 to 3 focus groups, each containing 8 to 12 individuals. To increase objectivity, focus group facilitators will be independent researchers who were not OHP facilitators. The pragmatic data analysis approach of Halcomb and Davidson [42] will be used for the purpose of focus group data analysis. In summary, identifying key passages and words will be independently analyzed, coded, and categorized (classifying key passages and words within themes) drawing on pragmatic thematic analysis to form emergent themes.

#### Statistical analyses

Intention-to-treat analyses will be employed to prevent overestimation of efficacy. Categorical variables will be analysed using chi-squared tests (or Fisher’s exact test for small samples). A mixed-effects model, repeated measures (MMRM) approach will be used to examine the longitudinal profile of continuous variables at 3, 6 and 12 months post-baseline. For all MMRM analyses, baseline scores will be used as covariates and the models will include prespecified fixed effects of treatment, clinician, and time, and treatment-by-time and treatment-by-clinician interactions.

Secondary analyses using analysis of covariance will be conducted to compare change scores during treatment and follow-up phases for primary, secondary, and process outcomes using the fixed, continuous covariate of baseline score as well as the categorical fixed effects of treatment group, clinician, and treatment-by-clinician interactions.

Although the attrition rate is not expected to vary by treatment condition, we will attempt to identify key predictors of attrition status (i.e. demographic and baseline clinical characteristics) and test for differences between conditions. Assuming the data are missing at random, several procedures offer effective approaches that may attenuate attrition. Maximum likelihood models (i.e. MMRM), with time as a random variable, allow the use of all available data from all assessments, reducing bias and increasing power [43]. In addition, multiple imputation procedures that utilise the expectation-maximization (EM) algorithm with bootstrap estimates of standard errors will be used to address attrition. The application of these procedures can provide unbiased estimates, even in the face of substantial missing data [44].

A full economic evaluation will occur alongside the proposed RCT. Healthcare outcomes and costs will be compared between participants in the control and interventional conditions. Healthcare system (medical record) and self-reported information via the HCUQ [30] will be used to generate analyses. The utility measurements of participant quality of life will be assessed using AQoL-6D [25] developed in Australia and the EQ-5D-3L [26] developed in Europe. The potential long-term (lifetime) impact on cost and effectiveness of intervention beyond the trial period will be extrapolated using the Markov process modelling method.

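### HADS caseness appears to be left to unadjusted chi-squared or Fisher tests; a baseline-adjusted longitudinal logistic model would use the data better (minor)

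*Protocol article*

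**What the plan says.** Protocol article, Statistical analyses: "Categorical variables will be analysed using chi-squared tests", or Fisher's exact test where samples are small. No covariate, visit or cluster term is attached to these tests, and no other method is given for categorical data.

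The next sentences bring in a mixed model for repeated measures (MMRM) to "examine the longitudinal profile of continuous variables at 3, 6 and 12 months post-baseline", and add: "For all MMRM analyses, baseline scores will be used as covariates". The same section sets the analysis principle ("Intention-to-treat analyses will be employed to prevent overestimation of efficacy"), assumes data missing at random, and states that "multiple imputation procedures that utilise the expectation-maximization (EM) algorithm with bootstrap estimates of standard errors will be used to address attrition".

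Outcome measurements lists among the secondary measures for survivors and carers "symptom severity and caseness of depression and anxiety disorders as assessed using the Hospital Anxiety and Depression Scale (HADS". Table 2 schedules HADS at baseline, 3, 6 and 12 months for both groups.

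**The concern.** HADS enters the plan in two forms: a severity score and a case/non-case classification. The score is continuous and gets a model that adjusts for baseline and uses all follow-up visits. The classification is categorical, and the only method named for it is a two-way table test. Such a test compares the arms at one visit at a time, cannot use the baseline score, and by itself yields a p-value rather than an effect estimate.

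At stake is precision on one secondary outcome. Depression and anxiety come first among the secondary objectives in Research aims, and caseness is a form in which clinicians may well read the result. If the baseline score predicts later caseness strongly, leaving it out costs power that is already low at this sample size.

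**Working it through.** **Inputs from the documents (Participants).** Effect size d = 0.50; two-tailed test at 0.05; 42 survivors and 42 carers per arm; up to 20 % attrition; correlation between baseline and post-treatment scores 0.81, given in a calculation for quality of life and self-efficacy, not for HADS.

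**Inputs assumed.** Control caseness 40 % (30 % as a variant); HADS baseline correlation 0.5, 0.7 or 0.81; treatment shifts the latent score by 0.5 SD. The documents give no caseness rate and no HADS correlation.

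**The plan's own figure.** No sample size is stated for a categorical outcome. The 53 per group is for the primary outcomes. It is nearly reproduced as a four-visit average: variance factor (1 + 3 × 0.81)/4 = 0.8575, so n = 2 × (1.96 + 0.842)² × 0.8575/0.5² ≈ 53.8. A larger correlation raises n in that formula, so it does not show that the sample size rests on baseline adjustment.

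**Step 1: number analysed.** 42 × 0.8 = 33.6, about 34 per arm for survivors or carers alone. Pooled, 84 × 0.8 = 67.2, about 67 per arm.

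**Step 2: chi-squared by formula.** With a case threshold 0.25 SD above the control mean, caseness is 1 − Φ(0.25) = 0.401 in controls and 1 − Φ(0.75) = 0.227 in the treated arm, a difference of 0.175.
- Null standard error: √(2 × 0.314 × 0.686/34) = 0.1126.
- Standard error under the alternative: √((0.401 × 0.599 + 0.227 × 0.773)/34) = 0.1106.
- Power ≈ Φ((0.175 − 1.96 × 0.1126)/0.1106) = Φ(−0.41), about 34 %.

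Simulation gives about 37 %, in fair agreement.

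**Step 3: simulated power at one visit, 34 per arm, 40 % control caseness.**

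| Assumed baseline correlation | Chi-squared | Logistic adjusted for baseline score |
|---|---|---|
| 0.5 | about 37 % | about 37 % |
| 0.7 | about 37 % | about 45 % |
| 0.81 | about 37 % | about 54 % |

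Null rejection was about 4–6 % for both methods.

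**Step 4: sensitivity.** A separate simulation of 1,000 trials per setting, with a likelihood-ratio test for the adjusted model and control caseness of 30–40 %, gave:

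| Per arm | Chi-squared | Adjusted, correlation 0.5 | Adjusted, correlation 0.81 |
|---|---|---|---|
| 34 | 31–37 % | 35–42 % | 50–59 % |
| 67 (pooled, treated as independent) | 56–62 % | 62–69 % | 77–84 % |

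The Monte Carlo standard error is about √(0.37 × 0.63/1000) = 1.5 points, and the choice of test also moves the adjusted figure a little. The gain is therefore nil to about 8 points at a correlation of 0.5, and roughly 17 to 25 points at 0.81.

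**Step 5: the severity score for comparison.** In the same simulation the undichotomised score, adjusted for baseline at one visit with 34 per arm, had power of about 63 % (correlation 0.5) or 92–94 % (0.81).

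**Limits.** The simulations cover one visit, with no dropout and no dyads. They measure the value of the baseline score only, not what the repeated visits would add.

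**The case against.** The sentence on categorical variables names no outcome and no visit. It may be meant for baseline tables, or for the comparison of attrition between conditions that the same section plans; chi-squared tests are ordinary there. This is a condensed article, and the model for a dichotomised secondary outcome can be left to an analysis plan. The HADS score already gets the MMRM, and both constructs with primary status, quality of life and self-efficacy, are analysed as continuous scores. The large power gap appears only at a correlation that the documents do not tie to HADS. All of this stands, and it keeps the point small. It does not remove it: the article does not leave the method open but names one, caseness is a declared outcome, and no other method in the text would cover it.

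Three stronger readings are tempting, and the documents do not support them.

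- *The tests contradict intention-to-treat or the missing-at-random assumption.* A chi-squared test can compare arms as randomised. The plan says "Assuming the data are missing at random, several procedures offer effective approaches that may attenuate attrition" and includes multiple imputation without restricting it to continuous variables.
- *Dropouts are discarded.* That would follow only from a complete-case test, and the text does not say the tests are complete-case.
- *Ignoring dyads loses power.* Patients and carers who take part together are randomised together (Randomisation and blinding), but clustering matters to this comparison only if survivors and carers are pooled, which is not stated. The harm would then be to type I error: for full dyads and an assumed intraclass correlation of 0.1 to 0.5, a nominal 0.05 test would run at about 0.062 to 0.110. The listed MMRM and covariance terms have no dyad effect either, so this is not specific to the categorical tests.

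**Conclusion.** The point holds as a minor matter of efficiency and consistency. On its most natural reading, the plan gives HADS caseness a valid but unadjusted test, while the continuous form of the same scale gets a baseline-adjusted longitudinal model. With 34 per arm and 40 % control caseness, adjustment for the baseline score changes power at one visit from about 37 % to between 37 % and 54 %, depending on a correlation that has to be assumed. At the low end there may be no gain at all. No primary conclusion is at risk, and no error in type I control follows from the chi-squared test itself when survivors and carers are analysed separately.

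**What to change.** State that HADS anxiety and depression caseness at 3, 6 and 12 months will be analysed with a logistic mixed model or GEE containing baseline HADS score, treatment, visit and treatment-by-visit, with clustering by dyad if survivors and carers are pooled. Say that the multiple imputation already planned applies to this analysis; this matters most for GEE, which without it needs a stricter missing-data assumption than the one the plan makes. Report odds ratios or risk differences with 95 % confidence intervals. Keep chi-squared and Fisher tests for descriptive comparisons.

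The cost is a change of wording and slightly more programming; no new data are needed. The main drawback is possible non-convergence where cases are sparse, so a simpler fallback model should be named in advance.

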### Participants

A total of 84 patients diagnosed with stroke, and 84 carers of these patients, will be recruited into the RCT. For the purposes of this study, stroke is defined as cerebral infarction or parenchymal haemorrhage confirmed by medical records. The following criteria are to be met for inclusion into the RCT: (1) diagnosis of stroke for patient or self-nominated carer of a stroke patient; (2) 18 years or older; (3) ability to converse in English without an interpreter or professional assistance; (4) absence of developmental disability or amnestic syndrome impairing their ability to learn from the intervention; and (5) absence of serious comorbid illness, including severe forms of aphasia, as identified by the nurse unit manager, and cognitive impairment, as identified from medical notes scoring lower than 24 on the Mini-Mental State Examination (MMSE) [27]. As the OHP adopts a holistic approach to managing chronic disease, patients may enter the program at any stage along the continuum of care.

Power was calculated to detect a medium effect size of Cohen’s *d* = 0.50. This was chosen as a clinically meaningful effect size that may be compared with previous RCT research in the area of chronic disease management programs [28]. Calculations assumed two primary outcomes (health-related quality of life and General Self-Efficacy Scale (GSE) scores), four assessment points (baseline, 3-month, 6-month, and 12-month), a study-wide type I error rate (α) of .05, and hence a type II error rate (β) of 0.20 (power of 0.80), a correlation of post-treatment scores with baseline measurements (ρ) of 0.81, and a two-tailed statistical test [29]. To detect an effect size of Cohen’s *d* = 0.50, 53 participants in each of the control and intervention groups will be required. Allowing for up to 20 % attrition, a total of 168 participants, or 42 carers and stroke survivors in control and intervention groups will be recruited.

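### The MMRM as listed fits one baseline slope for 3, 6 and 12 months; a baseline-by-visit term would be a cheap, minor improvement

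*Protocol article*

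**What the plan says.** All of this is in the protocol article.

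- **Statistical analyses, baseline term:** "For all MMRM analyses, baseline scores will be used as covariates".
- **Statistical analyses, fixed effects:** "the models will include prespecified fixed effects of treatment, clinician, and time, and treatment-by-time and treatment-by-clinician interactions". Two interactions are named, and baseline-by-time is not one of them. It is not expressly excluded either.
- **Statistical analyses, purpose:** the MMRM is meant to "examine the longitudinal profile of continuous variables at 3, 6 and 12 months post-baseline". No visit is singled out as primary.
- **Statistical analyses, secondary analyses:** "analysis of covariance will be conducted to compare change scores during treatment and follow-up phases for primary, secondary, and process outcomes", again with baseline as covariate.
- **Participants, sample size:** the calculation uses "a correlation of post-treatment scores with baseline measurements (ρ) of 0.81", one value for all post-treatment visits.
- **Participants, eligibility:** "patients may enter the program at any stage along the continuum of care".

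**The concern.** The listed model lets the treatment effect differ by visit but holds the regression on baseline constant. If a baseline score predicts the 3-month score better than the 12-month score, one slope cannot suit both visits. Under an unstructured covariance the common slope is then drawn towards the visits where baseline is most informative, so the 12-month comparison is adjusted too strongly for chance baseline differences.

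A weakening relation is plausible for survivors, because entry is open at any stage after stroke and some may still be recovering at baseline. The protocol reports no data on this.

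Two things could be at stake at the later visits: some precision and, if dropout is linked to baseline differently in the two arms, a small bias. The same model form is used for every continuous outcome, including both primary ones.

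**Working it through.** **1. The plan's own figure.** Inputs from Participants: d = 0.50, two-sided α = 0.05, power 0.80, ρ = 0.81, four assessments.

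- Plain two-sample size: 2 × [(1.960 + 0.842)/0.50]² = 62.8 per group.
- Variance factor for the mean of four measurements: (1 + 3 × 0.81)/4 = 0.8575.
- 62.8 × 0.8575 = 53.8 per group, and power at 53 is 0.794.

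This agrees with the stated 53 per group, although the authors' route is not certain. The figure does not depend on how baseline enters the MMRM, so the point below does not change it.

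**2. Variance at 12 months.** Assume unit SDs, complete data and independent participants. With treatment-by-time in the model, the 12-month estimate is

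(difference in mean 12-month score) − b × (difference in mean baseline),

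and its variance is proportional to (1 − r12²) + (r12 − b)², where r12 is the baseline to 12-month correlation.

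- With a baseline-by-visit term, b = r12 and the second part vanishes.
- With a common slope and unstructured covariance, b = (1ᵀS⁻¹r)/(1ᵀS⁻¹1). Here r holds the three baseline correlations, R is the between-visit correlation matrix, and S = R − rrᵀ.

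**3. The document's own input.** With r = 0.81 at every visit, b = 0.81 and the variance ratio is 1.000. Power for d = 0.50 at 53 per group is 0.992 with either model.

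**4. Assumed decay.** Neither the baseline correlations at 6 and 12 months nor the between-visit correlations (3–6 months 0.85, 6–12 months 0.80, 3–12 months 0.70) are in the document.

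| r at 3/6/12 months | b | 1 − r12² | (r12 − b)² | Variance ratio |
|---|---|---|---|---|
| 0.81/0.75/0.65 | 0.764 | 0.5775 | 0.0129 | 1.022 |
| 0.81/0.70/0.55 | 0.766 | 0.6975 | 0.0467 | 1.067 |
| 0.81/0.65/0.45 | 0.802 | 0.7975 | 0.1242 | 1.156 |

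Simulation with 34 and 67 per arm (about 80 % of 42 and of 84) gave ratios of 1.02, 1.06–1.07 and 1.14–1.15. When the slopes were equal the ratio was 0.99, so the interaction then costs about 1 %. At 34 per arm, 12-month power fell from 67.7 % to 65.5 % in the middle case and from 62.0 % to 56.6 % in the last.

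Other assumed between-visit correlations, at 53 per group, give the same picture for common against visit-specific slope:

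- 0.81/0.75/0.65: power 0.917 against 0.923
- 0.81/0.70/0.60: power 0.884 against 0.896
- 0.81/0.65/0.50: power 0.813 against 0.844

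**5. Bias with complete data.** In 10,000 simulated trials per setting at 53 per group, with a true effect of 0.50, the mean 12-month estimate was 0.498–0.503. Type I error with the common slope was 0.045–0.051. There is no bias and no inflation.

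**6. Bias with dropout.** Both models were fitted by maximum likelihood to 40,000 simulated participants. About 20 % were missing at 12 months, dropout depended on baseline only, and the true effect was 0.50. Monte Carlo error is about √(2 × 0.70/16,000) ≈ 0.01. Results for the three decays in the table's order:

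- Dropout related to baseline in one arm only: common slope 0.53, 0.53, 0.56; visit-specific slope 0.50–0.51.
- Dropout related to baseline in opposite directions by arm: common slope 0.55, 0.57, 0.60; visit-specific slope 0.50.
- The same dropout mechanism in both arms: no bias from either model.

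A further calculation of arm-differential dropout put the bias of the common slope at about 0.02–0.07 SD. The size depends on the assumed strength of the dropout relation.

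**The case against.** The strongest reply is that nothing in the article is shown to be wrong. Its only correlation implies equal slopes when the SDs are equal, and then the extra term is a small cost with no return. Decay is conjecture: open entry also admits long-term, stable survivors, and a wide mix of stages could raise the correlations. The stage-of-care argument says nothing about the 84 carers, who are half the sample. No covariance structure is stated, and no visit is named primary, so looking at 12 months picks the visit where assumed decay hurts most. The secondary analyses by phase fit their own baseline slopes and offer a partial check. Finally, a condensed article may leave such a term to an SAP that is not shown.

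Most of this stands, and it limits the point to a conditional one. Two things remain. The article does not leave the model open: it lists the effects and calls them prespecified, so an SAP that added the term would depart from that list. And the reassurance about bias rests on complete data, whereas the plan allows up to 20 % attrition and relies on a missing-at-random likelihood, which needs an adequate mean model.

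A reader might infer that the 12-month effect is in fact adjusted with a wrong slope, or that the trial's validity is at risk. The document gives no visit-specific correlations to support the first, and step 5 rules out the second for complete data.

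**Conclusion.** The point holds as a minor, conditional one. Read literally, the listed MMRM has one baseline slope for all visits. The effect on the 12-month estimate is nil if the slopes are equal, about 2–7 % in variance under mild to moderate decay, and about 16 % only if the correlation falls from 0.81 to 0.45. With complete data the estimate is unbiased and type I error holds. Bias of a few hundredths of an SD needs two conditions together: slopes that differ by visit, and dropout that depends on baseline differently by arm. It reached 0.10 SD only in the most extreme combination tried, the steepest decay with opposite dropout patterns.

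These sizes rest on assumed correlations, unit SDs, an unstructured covariance and independent participants; dyads and clinician terms were ignored.

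The single 0.81 in the sample-size paragraph might be read as a second error. It is a planning simplification and does not need correcting on this account.

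**What to change.** In Statistical analyses, add a baseline-by-visit interaction to the fixed effects of every MMRM and state that time is categorical there. The attrition paragraph of the same section speaks of time as random, so this is worth making explicit. Report treatment effects at 3, 6 and 12 months from that model.

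The change is one term in the plan and the code, to be made before analysis. The price is two degrees of freedom per model, about 1 % in variance if the slopes turn out equal. The sample size need not change.

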A health professional (e.g. nurse, psychologist) trained in the approach (2-day workshop plus regular supervision and fidelity checks) will facilitate each session. The facilitator will draw on carer and stroke-specific information in concordance with individual circumstances. Examples include the relationship between depression and caregiving or physical impairments of stroke, availability of stroke and carer supports in the community, and coping strategies for addressing anxiety and stress related to new roles and circumstances. The emphasis is on collaboration between facilitator and participant to arrive at goals for the program that stem from the participant’s main concerns and needs. The facilitator will encourage participants to identify their early warning signs of stress and illness and integrate healthy coping strategies to prevent the build-up of stress. Facilitators may also discuss and arrange referrals for other services in conjunction with the multidisciplinary team depending on participant needs. Additionally, facilitators will work with the multidisciplinary team to coordinate visits. Participants in rural and regional areas will have the option of participating in sessions via phone or Skype.

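### The primary MMRM and the ANCOVA cross an undefined clinician factor with treatment; if it means the SCOHP facilitator, the interaction is unidentified and the treatment coefficient depends on coding

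*Protocol article*

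**What the plan says.** The Statistical analyses section of the protocol article sets one mixed-model structure for all continuous outcomes, so it governs both primary outcomes (quality of life and self-efficacy). It states "For all MMRM analyses, baseline scores will be used as covariates" and lists as prespecified "fixed effects of treatment, clinician, and time, and treatment-by-time and treatment-by-clinician interactions". The secondary ANCOVA of change scores adjusts for baseline "as well as the categorical fixed effects of treatment group, clinician, and treatment-by-clinician interactions".

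Clinician is not defined in that section or in the abbreviation list. Other sections bear on what it can mean:

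- *Intervention: SCOHP*: sessions are led by "A health professional (e.g. nurse, psychologist) trained in the approach", called the facilitator from there on.
- *Control*: "The comparison group will receive usual care and no SCOHP intervention". Contact with the program comes later: "Participants in the control group will have the option of completing the SCOHP at the end of the trial once evaluation is complete".
- *Randomisation and blinding*: allocation is by computer-generated blocks. No stratification by clinician is described, and no control participant is linked to one.

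**The concern.** A treatment-by-clinician interaction asks whether the difference between SCOHP and usual care varies from one clinician to another. The data can answer that only if clinicians have participants in both arms. A facilitator has none in the control arm at 3, 6 or 12 months, so facilitator is nested within SCOHP.

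What is at stake is the treatment effect read from the primary model. The analyst would have to decide what clinician value a control receives and which level is the reference, and the software would decide which redundant columns to drop. These choices can change both the estimate and its precision. They would be made at analysis, in a trial whose participants and investigators know the allocation.

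**Working it through.** The plan gives no figure to reproduce here, so the check is on the structure of the stated model.

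**Inputs.** 84 participants per arm (*Participants*: 42 carers and 42 survivors in each group, 168 in all); visits at 3, 6 and 12 months; the fixed effects listed in *Statistical analyses*. The number of facilitators k is not given. I assume k = 2, 3, 4 and 6, with controls placed in a separate level, none.

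**Step 1: the treatment and clinician part alone.** The columns are an intercept, a treatment indicator T, k facilitator indicators C_j and k products T·C_j, which makes 2k + 2. Only k + 1 distinct cells exist (control, and SCOHP under each facilitator), so the rank is k + 1. The redundancies are T·C_j = C_j for each j (k of them) and ΣC_j = T (one more), a deficit of k + 1. At k = 4 this is 10 columns and rank 5.

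**Step 2: the full model.** Two visit columns, two treatment-by-visit columns and baseline add five columns and five to the rank, giving 2k + 7 columns and rank k + 6.

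| k (assumed) | Columns | Rank | Deficit |
|---|---|---|---|
| 2 | 11 | 8 | 3 |
| 3 | 13 | 9 | 4 |
| 4 | 15 | 10 | 5 |
| 6 | 19 | 12 | 7 |

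**Step 3: what can be estimated.** A contrast is estimable if it lies in the row space of the matrix. For every k tried:

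- Not estimable: the treatment coefficient, every clinician coefficient, every treatment-by-clinician coefficient, and a treatment difference averaged over clinician levels as in ordinary least-squares means.
- Estimable: differences between facilitators within SCOHP, and the mean over SCOHP facilitators minus control.

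**Step 4: what a printed treatment coefficient could be.** Suppose the software keeps T and drops one facilitator's column. The coefficient is then that one facilitator's participants minus all controls (at the reference visit). With equal caseloads of 84/k, independent observations and no attrition, the ratio of its standard error to that of the overall contrast is

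√[(k/84 + 1/84) / (2/84)] = √((k + 1)/2),

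which is √1.5 = 1.22 for k = 2, √2 = 1.41 for k = 3, √2.5 = 1.58 for k = 4 and √3.5 = 1.87 for k = 6. The arm size cancels, so the ratio is the same if carers and survivors are analysed separately.

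**Step 5: the other reading.** If each clinician has participants in both arms, columns and rank agree (9/9, 11/11, 13/13 and 17/17 for k = 2, 3, 4 and 6), and every term is estimable.

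**Step 6: after the change.** With facilitator nested in the SCOHP arm, and no crossed main effect or interaction, the averaged SCOHP-minus-control contrast is estimable for every k tried. As a fixed nested effect with equal caseloads, the facilitator average has variance proportional to (1/k²)·k·(k/84) = 1/84, the same as the plain arm mean.

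**The case against.** The strongest objection is that clinician is undefined and need not mean facilitator. The article uses *facilitator* for the person delivering SCOHP. It uses *clinician* for senior staff consulted on eligibility (*Consent*) and for the several professionals whom patients and carers deal with (*Discussion*). A treating clinician seen in both arms would give a full-rank model, and the definition may sit in a document not shown. This stands, and it makes the point conditional. But the usage is mixed: the TRIPOD background section and *Program assessment and treatment fidelity* link clinicians with delivering the program, and no clinician is described for controls. Nor can a later definition of clinician as facilitator rescue a crossed interaction.

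It would also go too far to say that carers and community recruits have no clinician. The article says that usual care will vary, not that it is absent. What it lacks is a rule giving each of them one clinician value.

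A reader might infer that the primary analysis cannot deliver a valid treatment effect at all. The documents do not support this. Redundant columns leave the fitted values unchanged, and the averaged contrast is recoverable. Coding clinician as missing for controls would delete all 84 of them from a complete-case fit, but the article does not propose that, and it would conflict with its intention-to-treat commitment.

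A reader might also infer an inflated type I error from ignored facilitator clustering. That describes a different model. On the facilitator reading, the stated fixed effects absorb facilitator differences, with inference conditional on these facilitators.

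**Conclusion.** The point holds conditionally. On the reading the article best supports, clinician is the SCOHP facilitator. The stated primary model and the ANCOVA then cross a factor that exists in one arm only: the model is short of full rank by k + 1, the interaction cannot be identified, and the treatment coefficient has no fixed meaning until coding and reference level are chosen. The SCOHP-minus-usual-care contrast averaged over facilitators survives but is not named as the target.

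The rank result needs only that facilitators see no controls before evaluation ends. The standard-error ratios of 1.22 to 1.87 rest on assumed k from 2 to 6 and equal caseloads, and apply only if a single reference-facilitator coefficient is reported as the trial result. If clinician means someone present in both arms, the algebra is sound and the remaining defect is the missing definition. Either way the text needs correction before outcomes are analysed.

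**What to change.** If clinician means the facilitator:

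1. Remove the crossed clinician main effect and the treatment-by-clinician interaction from the primary MMRM and from the ANCOVA.
2. State the target as SCOHP minus usual care averaged over facilitators, and say whether facilitators are weighted equally or by caseload.
3. Account for facilitator by a term nested in the SCOHP arm only. This can be a partially nested random effect with small-sample degrees of freedom, or a fixed nested effect if facilitators are few. The choice is one of inference: the first generalises to other facilitators, the second is conditional on those in the trial.

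If clinician means a treating clinician present in both arms, keep the terms but define the factor, including its value for carers and community recruits.

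**Cost.** The change is to analysis wording; it needs no new data and does not by itself alter the sample size. Intervals may widen, and with a random effect and very few facilitators they may widen a great deal. Where facilitator variance matters, the degrees of freedom can fall towards k − 1, with a critical t of about 12.7 on 1 degree of freedom (k = 2) and 3.2 on 3 (k = 4). A fixed nested effect avoids most of that loss. Neither option deals with correlation within survivor–carer dyads, which is a separate matter.
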